## Methods

### Study Design

This is a pragmatic two-arm cluster randomized trial evaluating the effectiveness GSP delivered by trained LHWs to persons with HIV presenting with mild to moderate depression in primary care. The study involves LHWs affiliated to 30 primary care health centers (PHCs) in three districts in northern Uganda. Eligible PHCs were randomly assigned (1:1) to have their LHWs trained in the delivery of GSP (intervention) or GHE (control) to PLWH with mild to moderate depression. PLWH treated by trained LHWs will be evaluated at baseline, at the end of intervention, and at intervals of 6 months thereafter for 2 years.

A longitudinal process evaluation of the delivery of GSP by trained LHWs using mixed methods will run alongside the trial to assess acceptability, feasibility, fidelity, and how intervention recipients respond to the different intervention components. Analysis is performed according to the intention-to-treat (ITT) principle and will account for the cluster randomized design. The study protocol is registered in the Pan African Clinical Trials Registry (PACTR201608001738234), and the reporting of the trial will be in accordance with the Standard Protocol Items: Recommendations for Interventional Trials (SPIRIT) guidelines [28] for intervention trials (see Multimedia Appendix 1) and the CONSORT statements for cluster randomized trials [29].

The study was submitted to and approved by both the Makerere University College of Health Sciences Research Ethics Committee and the Uganda National Council of Science and Technology. All study participants will be required to provide written informed consent. Light refreshments will be served during all group sessions in both arms, and every participant will receive a financial incentive to defray transport costs. Figure 1 summarizes the trial profile.

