### Participants

#### Cluster Eligibility Criteria, Recruitment, and Randomization

To be eligible for the trial, the primary care health centers had to offer HIV care and treatment services, nominate at least four LHWs (2 men and 2 women) who are actively involved in HIV care, able to read and write, and reside within the villages served by the PHC. PHCs that do not offer HIV care services and those unable to nominate literate LHWs were excluded from the study.

To recruit PHCs, the project team worked with the district health officials in each of the three participating districts and identified a total of 38 PHCs that offered HIV care and treatment services. The health center managers of these centers were informed about the trial and asked to nominate health workers to participate in the trial. The first 10 PHCs in each district that expressed interest in the trial and nominated the required number of health workers were recruited to the trial. The health center managers of the 10 eligible PHCs in each district were invited to a stakeholders’ meeting held at the district’s local government offices with political leaders, district health officials, religious leaders, and community leaders. Study purpose and procedures were explained to facilitate district leadership understanding of the trial activities. At the end of the meeting, the eligible PHCs were randomly allocated with a 1:1 ratio to intervention and control arms. Randomization was done by urn randomization picked by each health center manager or their representative who attended the stakeholders’ meeting.

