### Statistical Analyses

We will assess randomization across the two arms by comparing sociodemographic characteristics and other potential confounding variables using chi-square for categorical variables, and *t* tests or other equivalent nonparametric tests, as appropriate, for continuous variables. Primary outcomes will be the difference in follow-up proportions of participants who meet MINI criteria for major depression and difference in follow-up function scores of participants in the intervention and control arms 6 months after the end of treatment.

Secondary outcomes will include measures of self-esteem, posttraumatic stress symptoms, social support, stigma, alcohol use, ART adherence, viral load, number of disability days, asset possession indices, and cost-effectiveness data. Primary outcomes, secondary outcomes, and all subgroup analyses will be analyzed by ITT using a multilevel mixed model adjusting for clustering in health centers to determine effect modifiers [49]. The status of randomization (intervention/control) and baseline depression score will be included as a covariate. To account for the clustered design, we will treat clusters as a random effect. Potential confounding variables (eg, age, gender, socioeconomic status) with significant differences across intervention and control arms will be included as fixed factors. The R statistical software will be used to conduct all analyses [50]. A process evaluation using mixed methods to assess acceptability, feasibility, fidelity, causal mediating processes, and contextual influences in the trial will be conducted.

The primary analysis will follow ITT principles and use all available follow-up data, with missing data handled directly through maximum likelihood estimation in mixed modeling. We will document the extent and pattern of missing data and the reasons and will conduct sensitivity analyses of the impact of missing data on stability of the primary results. Missing values will be imputed with multiple imputations. We will verify that mixed model‒based results are not sensitive to violations of model assumptions with permutation tests.

Last, Cohen *d* effect sizes will be computed for the effect estimates to determine the size of the intervention effect [51].

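### Health centers were allocated separately within three districts, but the named model terms leave district out; if districts differ in outcome, some precision is lost

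*Protocol article*

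**What the plan says.** The design is described under Cluster Eligibility Criteria, Recruitment, and Randomization. "The first 10 PHCs in each district that expressed interest in the trial and nominated the required number of health workers were recruited". The next step was also taken district by district ("The health center managers of the 10 eligible PHCs in each district were invited to"): the gathering was held in the offices of that district's own local government. On the allocation itself the section says: "At the end of the meeting, the eligible PHCs were randomly allocated with a 1:1 ratio to intervention and control arms". The method was an urn draw. With three districts and 30 centers (Study Design: "The study involves LHWs affiliated to 30 primary care health centers (PHCs) in three districts in northern Uganda"), this is three separate 1:1 draws of ten. The section does not use the word stratified and does not state a 5:5 split, but the procedure implies both.

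The model is described under Statistical Analyses. For clustering, the section says: "To account for the clustered design, we will treat clusters as a random effect". For covariates, it says: "The status of randomization (intervention/control) and baseline depression score will be included as a covariate". Other potential confounders enter only on a condition: those "with significant differences across intervention and control arms will be included as fixed factors". District is not among the named terms. The same section plans to verify that mixed-model results are "not sensitive to violations of model assumptions with permutation tests", without saying how arm labels will be permuted.

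The Sample Size and Power Calculations section treats the clusters as unmatched and makes no allowance for stratification.

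**The concern.** When allocation is balanced within districts, differences between districts cancel out of the treatment contrast. An analysis that omits district does not take credit for this. It estimates the between-PHC variance from all 30 centers together, so any district variation is counted as noise. The standard error then exceeds the true sampling variability of the estimate, and some of the precision that the design bought is not used.

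The covariate rule makes the omission more than a matter of brevity. With five centers per arm in each district and a target of 40 participants per center, each district would contribute about 5 × 40 = 200 participants to each arm. A baseline test of district against arm would then be near zero by construction. A rule that admits only significantly different variables therefore tends to keep out the one factor that the allocation used.

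Precision is at stake for both primary outcomes and all secondary outcomes, in a trial with 30 independent units. Validity is not.

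**Working it through.** **Inputs from Sample Size and Power Calculations:** p0 = 0.25, p1 = 0.15, between-cluster coefficient of variation k = 0.25, m = 32 analyzed per cluster (40 enrolled, 20% loss), 12 clusters per arm in the calculation and 15 used, alpha 5%. Two-sided testing is not stated but reproduces the table.

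**Step 1: reproduce the plan's figure.** Variance of the difference, per cluster pair:

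- sampling part: (0.25 × 0.75 + 0.15 × 0.85)/32 = 0.315/32 = 0.009844
- between-cluster part: 0.25² × (0.25² + 0.15²) = 0.0625 × 0.085 = 0.005313
- total: 0.015156

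Clusters per arm = (1.960 + 0.842)² × 0.015156/0.10² = 11.90, rounded up to 12. Power at 12 = Φ(√(12 × 0.01/0.015156) − 1.960) = 0.8034, against 0.803 in Table 2. All eight rows of Table 2 reproduce this way (without the extra cluster that is sometimes added). At 15 clusters per arm the same formula gives 0.882.

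**Step 2: split the between-cluster part.** Let f be the share of between-PHC variance that lies between districts. The documents do not give f, so a range is shown. With a 5:5 split in each district:

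- half-width without district: t(28 df) × √(0.015156/15) = 2.048 × 0.03179 = 0.0651
- half-width with district: t(26 df) × √([0.009844 + (1 − f) × 0.005313]/15)

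Example, f = 0.50: 2.056 × √(0.012500/15) = 2.056 × 0.02887 = 0.0593, and 0.0651/0.0593 = 1.097 from unrounded values.

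**Step 3: simulate.** Cluster proportions were simulated for 30 PHCs, 5:5 in each of three districts, with 2,000 runs per setting. Each simulated data set was analyzed with and without district as a fixed effect. Monte Carlo error is about 0.5 to 0.8 points on each power figure.

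| District share f (assumed) | Half-width ratio, without/with district | Model power, without v with | Permutation power, unrestricted v within district |
|---|---|---|---|
| 0 | 0.997 | 0.880 v 0.882 | 0.861 v 0.860 |
| 0.10 | 1.014 | 0.881 v 0.885 | 0.862 v 0.864 |
| 0.25 | 1.043 | 0.884 v 0.892 | 0.860 v 0.872 |
| 0.50 | 1.097 | 0.893 v 0.921 | 0.874 v 0.899 |
| 0.75 | 1.161 | 0.898 v 0.934 | 0.883 v 0.924 |

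With no treatment effect (25% in both arms), type I error without v with district was 0.049 v 0.047 at f = 0, 0.038 v 0.046 at f = 0.25, and 0.034 v 0.047 at f = 0.50.

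The simulation uses cluster summaries as a stand-in for the planned mixed model, without the baseline depression score.

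**The case against.** The strongest reply is that the loss is conditional and small. No between-district variance is given, and the Study Setting section describes the three districts together, with the same war, poverty and livelihoods. If districts carry 10% of the variance, intervals are 1.4% wider and power moves by 0.4 points, which is close to simulation noise. Even at larger shares the unadjusted model has power of 0.88 or more. This stands, and it limits the size of the point. It does not defend the omission, because including district costs almost nothing when districts are alike (ratio 0.997).

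A reader might infer several stronger things that the document does not support.

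- **That the permutation test ignores district.** The article gives no permutation scheme, and a condensed article commonly leaves that to the full plan. Silence is not evidence of an unrestricted test.
- **That the loss is large.** With an intracluster correlation of 0.05 and half of the between-PHC variance at district level, a similar simulation gave power of 0.830 without district and 0.917 with it. But ICC = k²p/(1 − p), so 0.05 implies k of about 0.39 at 25% and 0.53 at 15%. The protocol's k = 0.25 implies about 0.021 and 0.011.
- **That the planned MINI test will be conservative overall.** The type I figures above come from cluster summaries with a t reference. A separate run of a maximum-likelihood logistic-normal model with a Wald z test and 15 clusters per arm rejected in 6.6% to 7.1% of 1,500 null runs. That small-sample effect pulls the other way and was not combined with the omission of district, so the net error rate is not established here.

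**Conclusion.** The point holds as a matter of efficiency. Allocation was done within district, the named model terms omit district, and the covariate rule would not be expected to bring it in. The estimate is not biased, and this omission does not inflate type I error.

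On the protocol's own assumptions for the MINI outcome, intervals are about 1% to 10% too wide and about 0.4 to 3 points of power are lost if districts carry 10% to 50% of between-PHC variance. The loss is zero if they carry none. Nothing here suggests that the trial falls below its planned 80% power.

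These figures rest on three things: the assumed district share, the implied 5:5 split, and cluster summaries standing in for the mixed model. They apply to MINI depression only. The sample size section gives no variance for the function score, so the size of any loss for that primary outcome cannot be worked out from the document.

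**What to change.** Add one sentence to the analysis: district (three levels) enters every primary and secondary model as a fixed effect because allocation was done within district, whether or not it differs between arms at baseline. State also that the planned permutation tests re-allocate arm labels at PHC level within district. If each district split 5:5, that leaves 252³ = 16,003,008 possible allocations, which is ample. Confirm the actual split in each district when reporting the allocation.

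The cost is 2 degrees of freedom (28 to 26 on the cluster-summary scale) and no new data. The Results section says that analysis of the 6-month data is in progress, so the wording should be fixed and dated before results by arm are seen. Small-sample inference for the mixed model is a separate question that this change does not settle.

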#### Participant Eligibility Criteria, Recruitment, and Masking

To be eligible for the study, PLWH had to be 19 years and older, diagnosed with major depression assessed with the MINI depression module [32], antidepressant naïve, using ART, and residing in the villages where the trained LHWs lived. Individuals with high suicide risk [33], a severe medical disorder such as pneumonia or active tuberculosis, psychotic symptoms, and hearing or visual impairment were excluded from the study.

On a given clinic day, project research assistants worked with primary care health workers of a participating PHC in the center’s HIV clinic. The primary care health worker gave a health talk on depression to clients in the waiting area. Clients who felt that they had experienced symptoms of depression described in the health talk were invited for further evaluations using the Luo version of the 20-item self-reporting questionnaire [34] and the MINI depression module. This procedure was repeated until a total of 40 PLWH diagnosed with major depression were obtained from a given PHC.

Clients diagnosed with major depression were approached by research assistants who explained study procedures, determined eligibility, and then obtained informed consent. Each client who gave informed consent received baseline assessments with a standardized questionnaire. Recruited participants from the same village were assigned to a trained LHW residing in or near their village to receive the intervention they had been trained to deliver (ie, either GSP or GHE).

By design, both experimental and control interventions were identifiable to participants but will be masked to outcome assessors, the Data and Safety Monitoring Board, and data analysts.

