## Results

The trial has been approved by the Makerere College of Health Sciences School of Health Sciences Research Ethics Committee, TASO, and the Uganda National Council of Science and Technology. A Data and Safety Monitoring Board has been put in place to monitor trial progress. A total of 1140 persons living with HIV have been recruited to the trial. An analysis of baseline and 6-month data is in progress.

The results of this trial will not only be presented at national and international conferences but also submitted for publication in peer-reviewed journals and as a report to the funding agencies.

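### Apart from baseline depression score, covariates for the outcome models are chosen by baseline significance tests with no stated allowance for clustering

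*Protocol article*

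**What the plan says.** All of this is in the protocol article, Statistical Analyses.

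- Balance between arms is assessed by "comparing sociodemographic characteristics and other potential confounding variables using chi-square for categorical variables", and by t tests or nonparametric equivalents for continuous variables. No adjustment of these tests for health center is mentioned, and no threshold for significance is given.
- Two terms are fixed in advance: "The status of randomization (intervention/control) and baseline depression score will be included as a covariate".
- The rest depend on the tests: "Potential confounding variables (eg, age, gender, socioeconomic status) with significant differences across intervention and control arms will be included as fixed factors". The list is given by example, so it is open.
- The resulting models cover everything that matters: "Primary outcomes, secondary outcomes, and all subgroup analyses will be analyzed by ITT using a multilevel mixed model adjusting for clustering in health centers".
- Clustering is dealt with in the outcome models: "To account for the clustered design, we will treat clusters as a random effect".

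The section on cluster eligibility, recruitment and randomization confirms that health centers, not people, were allocated 1:1. Table 1 shows that functioning, a co-primary outcome, is measured at baseline.

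**The concern.** There are three defects in the rule as written.

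1. **The test does not match the design.** A chi-square or t test on individuals treats people from one center as independent. Where a characteristic is clustered by center, chance differences between arms are larger than the test expects, so it declares too many of them significant.
2. **The criterion is the wrong one.** Whether a covariate is worth adjusting for depends on how well it predicts the outcome, not on whether its imbalance passes a threshold. A strong predictor that is mildly imbalanced is left out, and a weak one that passes goes in. The clearest case is baseline function, which is not among the fixed covariates and so could enter the function model only through this screen.
3. **The primary model is not fixed.** With an open list and no stated threshold, the covariates in both primary analyses are unknown until arms have been compared at baseline. The article reports that "An analysis of baseline and 6-month data is in progress", so there is little time left to settle this.

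At stake are the precision of the primary estimates and a clear statement, made in advance, of which model gives the primary result.

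**Working it through.** **Inputs from the protocol.** 1140 recruited in 30 centers, so 1140/30 = 38 per center; 15 centers per arm; between-cluster coefficient of variation k = 0.25; assumed 6-month proportions 0.25 and 0.15; cluster size 32 for the calculation. **Assumed:** a 5% two-sided threshold for the baseline tests, and the ICC of the baseline covariates, which the protocol does not give.

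**Step 1: the plan's own figure.** The unmatched cluster formula gives, per arm,

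c = (1.96 + 0.84)² × [p0(1−p0)/m + p1(1−p1)/m + k²(p0² + p1²)] / (p0−p1)².

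With m = 32, the bracket is 0.1875/32 + 0.1275/32 + 0.0625 × 0.085 = 0.01516. Then c = 7.85 × 0.01516/0.01 = 11.90, so 12 clusters with power 0.803, as in Table 2. All eight rows of the table match. This confirms that k enters as a between-cluster variance of k²p².

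**Step 2: a guide to the ICC.** Dividing k²p² by p(1−p) gives ICC = k²p/(1−p).

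- p = 0.15: 0.0625 × 0.15/0.85 = 0.011
- p = 0.25: 0.0625 × 0.25/0.75 = 0.021

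These are outcome ICCs. Baseline covariates may differ, so 0.05 is shown as well.

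**Step 3: chance rejection by one individual-level test.** The design effect is DE = 1 + (38−1) × ICC, and the rejection rate with no systematic difference between arms is 2[1 − Φ(1.96/√DE)]. Simulated values come from 20,000 runs with 15 clusters of 38 per arm.

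| ICC | DE | Formula | Simulated, continuous | Simulated, binary |
|---|---|---|---|---|
| 0 | 1.00 | 5.0% | 4.9% | 5.0% |
| 0.01 | 1.37 | 9.4% | 9.2% | 9.0% |
| 0.02 | 1.74 | 13.7% | 13.8% | 13.9% |
| 0.05 | 2.85 | 24.6% | 24.3% | 24.8% |

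A t test on the 15 versus 15 center means rejected 4.9% to 5.1% of the time in the same simulations (ICC up to 0.10), so the excess comes from ignoring the clusters.

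**Step 4: the three covariates that the protocol names.** If they are independent, the chance that at least one is selected is 1 − (1 − rate)³, using the simulated continuous rates:

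- ICC 0: 1 − 0.951³ = 14%
- ICC 0.01: 1 − 0.908³ = 25%
- ICC 0.02: 1 − 0.862³ = 36%
- ICC 0.05: 1 − 0.757³ = 57%

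**Step 5: what this does to the treatment effect.** A separate simulation used three covariates, a continuous outcome with an assumed ICC of 0.02, no treatment effect and tests on cluster means, as a simplification of the planned mixed model (4,000 runs per setting; covariate ICC 0.02 to 0.10; coefficients 0.1 or 0.3). Under the selection rule, type I error was 3.1% to 5.2% and mean bias was at most 0.0024 SD. The standard deviation of the estimate, rule versus adjustment for all three, was:

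- covariate ICC 0.02, coefficient 0.1: 0.0768 versus 0.0765, almost no loss
- covariate ICC 0.05, coefficient 0.3: 0.0824 versus 0.0773, a ratio of 1.07, or about 7% wider

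**The case against.** The strongest reply is that little follows for the primary result. A false positive in the screen only adds a baseline covariate to a model that already has a random effect for center. Baseline depression score, a likely strong predictor of the depression outcome, is in the model regardless. Selection looks at baseline data, not outcomes, and the protocol masks its data analysts. Participants were recruited after centers were allocated, so looking at balance is reasonable. The final covariate list might also sit in an analysis plan that is not shown.

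Most of this stands, and it rules out several stronger readings:

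- A reader might infer that the whole adjustment set is data-driven. It is not, because baseline depression score is fixed in advance.
- A reader might take the rejection rates in Step 3 as the false-positive rate of the trial. They describe the baseline screen only. Step 5 shows no material inflation for the treatment effect, and a conservative test when covariates are strong.
- A reader might multiply the rates over a long list of characteristics at a high ICC and reach near certainty of a false selection. The protocol names three covariates, and its own k points to an ICC near 0.01 to 0.02.
- A reader might infer systematic imbalance, since "The primary care health worker gave a health talk on depression to clients in the waiting area" and health workers at the centers received arm-specific training. The documents do not say that the worker giving the talk was one of those trained.
- A reader might infer from the ongoing 6-month analysis that outcomes guide the choice of covariates. Nothing says so.

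The appeal to an unseen plan does not stand. The selection rule is stated here, so this is a rule fixed badly and not a detail left out. The permutation tests in the same section check model assumptions, not covariate choice. And a wish to examine balance is met by a descriptive table.

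**Conclusion.** The concern holds in limited form. The protocol selects every covariate other than baseline depression score by a test that, as named, ignores the unit of randomization and does not measure prognostic value. That screen would run at about 9% to 14% instead of 5% at an ICC of 0.01 to 0.02, and about 25% at 0.05. In practice, baseline function may be missing from the co-primary function model, and some precision is lost when the covariates predict the outcome (about 7% in one simulated setting, close to nothing in another).

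This rests on the baseline tests being unadjusted, which follows from the tests named but is not said outright; on a 5% threshold; on assumed ICCs for the covariates; and, for the joint figures, on independence. Allocation appears to have been done district by district, which would lessen the inflation if clustering arises mainly between districts. Bias or an inflated type I error in the treatment effect is not shown.

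**What to change.** Delete the significance-based selection rule and the baseline tests that feed it. Present baseline characteristics by arm descriptively. Before arm labels are opened, name one covariate set to be used whatever the balance:

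- the baseline depression score already planned, with its instrument stated (Table 1 lists the Self-Reporting Questionnaire for depression symptoms);
- the baseline function score, for the function outcome;
- age and gender;
- the baseline socioeconomic or poverty index;
- district, since the account of the stakeholders' meetings indicates allocation within district.

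Do not add baseline MINI status: everyone enrolled meets the criterion by eligibility, so it is constant and cannot be fitted.

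The cost is a change of wording. The individual-level terms use a few degrees of freedom among about 1140 × 0.8 = 912 expected at follow-up. District is a cluster-level factor and uses two degrees of freedom out of 30 clusters. No new data are needed.

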### Sample Size and Power Calculations

Primarily, our objective is to compare the proportion of subjects with mild to moderate depression in the intervention and control arms 6 months after the end of treatment. Based on results from our pilot project, we assume that the difference in proportion of depression cases at 6 months follow-up between intervention (15%) and control arms (25%) would be 10%. Using formulae proposed by Hayes and Moulton [48], and assuming the between-cluster coefficient of variation *k* of .25, a study with 12 nonmatched pairs of clusters, and a cluster size of 32 PLWH (total expected sample size of 768 PLWH) would have 80% power of detecting a 10% reduction in major depression cases at the 5% significance level. Table 2 illustrates the sample size and power calculations for various assumptions made. The number of clusters has been increased to 15 pairs to allow for individual level analyses using multilevel random effects regression models, and the cluster size was increased to 40, accounting for a potential 20% loss to follow-up.

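### The primary mixed model is to be fitted by maximum likelihood on 30 clusters with no small-sample correction stated; uncorrected Wald tests at 5% would run at roughly 6-7%

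*Protocol article*

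**What the plan says.** Statistical Analyses in the protocol article plans a multilevel mixed model for the primary outcomes, with health centers as a random effect and arm and baseline depression score as covariates. Its paragraph on the primary analysis names the estimator in a clause about missing data: "missing data handled directly through maximum likelihood estimation in mixed modeling". The same paragraph plans permutation tests to verify that the mixed-model "results are not sensitive to violations of model assumptions with permutation tests". It names no test statistic, reference distribution or degrees-of-freedom rule, and it does not say whether centers or individuals would be permuted.

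Sample Size and Power Calculations gives the reason for the final number of clusters: "The number of clusters has been increased to 15 pairs to allow for individual level analyses using multilevel random effects regression models". The calculation behind it is "a study with 12 nonmatched pairs of clusters, and a cluster size of 32 PLWH (total expected sample size of 768 PLWH"), for "80% power of detecting a 10% reduction in major depression cases at the 5% significance level".

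**The concern.** Arm is assigned to health centers, so the arm effect is tested against variation between centers. With 30 centers and two arm means, that comparison has 28 degrees of freedom, however many people are assessed. Maximum likelihood (ML) takes no account of the two means having been estimated. For balanced clusters it divides the between-cluster sum of squares by 30 instead of 28, so the standard error is too small. A normal or chi-square reference adds a second error in the same direction.

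At stake are the type I error and interval width for both primary outcomes. The permutation test could protect the error rate, but as a check on assumptions it replaces neither the primary p value nor the confidence interval.

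**Working it through.** **Inputs.** Two-sided level 5%; 25% versus 15%; k = 0.25; 12 clusters per arm of 32 in the calculation; 15 clusters per arm in the trial (all from Sample Size and Power Calculations and Table 2). The Results section reports 1140 recruited: 1140/30 = 38 per center, or 38 × 0.8 = 30.4 after the planned 20% loss. The article gives no ICC, so for the continuous outcome I assume a range of 0.005 to 0.10. For the binary outcome, ICC = k²p/(1 − p), which is 0.021 at 25% and 0.011 at 15%.

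**1. The plan's own figure.** With the Hayes-Moulton unmatched formula:
- V = p0(1 − p0)/m + p1(1 − p1)/m + k²(p0² + p1²) = 0.1875/32 + 0.1275/32 + 0.0625 × 0.085 = 0.01516.
- c = (1.96 + 0.842)² × 0.01516/0.10² = 11.90, rounded up to 12.
- Power = Φ(√(12 × 0.01/0.01516) − 1.96) = 0.803, as in Table 2.

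All eight rows of Table 2 reproduce this way, from normal quantiles and without the formula's extra cluster per arm (which would give 12.90, so 13). The calculation therefore contains no small-cluster allowance. The 15 clusters per arm more than cover that.

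**2. Closed-form level, continuous outcome, balanced clusters.** T is t-distributed on 28 df.
- ML, Wald z: P(|T| > 1.96 × √(28/30)) = P(|T| > 1.893) = 6.9%.
- ML, likelihood ratio: reject if 30 × ln(1 + T²/28) > 3.841, that is |T| > 1.956, giving 6.1%.
- REML, z: P(|T| > 1.96) = 6.0%.
- ML, t on 28 df: P(|T| > 2.048 × √(28/30)) = 5.8%.
- REML, t on 28 df: 5.0%.
- Interval width, ML with z, relative to the correct one: 1.96 × 0.966/2.048 = 0.924, so 7.6% too narrow.

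**3. Simulation, linear model, 30 per cluster.** When the variance estimate can be truncated at zero, the excess shrinks at low ICC (200,000 runs per ICC).

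| ICC | ML, z | REML, t28 |
|---|---|---|
| 0.005 | 5.3% | 3.9% |
| 0.01 | 6.0% | 4.5% |
| 0.02 | 6.6% | 4.9% |
| 0.05 | 6.9% | 5.1% |
| 0.10 | 6.8% | 4.9% |

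**4. Simulation, depression, random-intercept logistic model by ML, about 30 per cluster.** The Monte Carlo standard error is about 0.5 points.
- Normal random intercepts, k = 0.25: Wald z 5.9-6.0%, likelihood ratio 5.4-5.5%. At k = 0.5: 6.7% and 6.0%.
- Beta-binomial clusters at 25%, k = 0.25: Wald z 6.9%, t reference 5.7%, cluster-level t test 5.0%. At k = 0.4: 6.2%, 5.3% and 4.4%.

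The two sets do not agree closely at k = 0.25, so the binary figure is best read as about 6-7%.

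**5. District balance.** Cluster Eligibility Criteria, Recruitment, and Randomization describes ten centers per district, drawn at district meetings with 1:1 allocation. If that meant five and five (an assumption) and the model omits district, ML with z gives 5.9% when district is 10% of the between-cluster variance and 4.4% when it is 30%.

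**6. Power after correction, 15 per arm.** With 32 analysed per cluster, the noncentrality is √(15 × 0.01/0.01516) = 3.146. Power is 88.2% by z and 85.9% by t on 28 df. With 30.4 analysed it is about 87% and 85%.

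**The case against.** The strongest reply is that the 6.9% needs both full maximum likelihood and a Wald z reference, and the article states only the first, in a clause about missing data. Test statistics and degrees-of-freedom rules are commonly left to an analysis plan, and a journal article condenses the protocol. A reader might infer that the trial is committed to uncorrected Wald inference, or that its 5% test does run at 6-7%. The text supports neither, so the figure must stay conditional.

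Three further parts of the reply stand. The excess is 1-2 points at most and depends on ICC and test statistic. With district balance ignored in the model, even its direction is open. And the authors did consider cluster numbers for this model and did plan permutation tests, which would hold the level if centers are the units permuted.

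The reply does not remove the point. The estimator is stated, not absent, and the sentence that names it describes the primary analysis. For the continuous outcome, a later choice of t reference would reduce the excess but leave 5.8% in closed form as long as ML is kept. The missing-data aim does not require that choice, because REML also uses all available follow-up data. The permutation test has a stated role, and that role is a check.

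**Conclusion.** The point holds as a conditional one. With ML on 30 clusters and no correction, the nominal 5% test would run at roughly 6-7% with Wald z, and the continuous-outcome interval would be up to about 7-8% too narrow. The closed-form figures assume balanced clusters, no cluster-level covariates and no district effect. At ICC 0.005 the simulated Wald z level is 5.3%.

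This does not show that the trial's error rate is in fact inflated. It shows that the stated estimator is poorly suited to the number of clusters, and that the planned method which would protect the level has been given a secondary role. Priority is modest.

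**What to change.** - **Function scores:** fit by REML, with Kenward-Roger or Satterthwaite degrees of freedom for the arm effect and its interval.
- **MINI depression:** make the already planned permutation test the primary p value, permuting health centers, within district if allocation was done that way. At the least, use a t reference with between-cluster degrees of freedom (28, or fewer if district is fitted). In the beta-binomial simulation this gave 5.3-5.7%, so it reduces the excess without fully removing it.
- **Wording:** state the unit of permutation and whether district is in the model.

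The cost is a few sentences and a software option. A permutation p value does not itself supply an interval, so the plan should also say how the interval is obtained: by inverting the test, or from the model with the t reference. Using t on 28 df, power for 25% versus 15% falls by about 2 points to about 85%, still above the 80% target. The article says the analysis of 6-month data was already in progress, so the rule should be fixed before the arm comparison is known, and its timing recorded.
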